## Abstract

**Background:**

Frequent chronic obstructive pulmonary disease (COPD) exacerbation is a major cause of hospital admission and mortality. It has been reported that Traditional Chinese Medicine (TCM) may relieve COPD symptoms and reduce the incidence of COPD exacerbations, thus improving life quality of COPD patients. The acute exacerbation of COPD risk-window (AECOPD-RW) is the period after an exacerbation and before the patient returns to baseline. In the AECOPD-RW, patients are usually at increased risk of a second exacerbation, which may lead to hospital admission and high mortality. It may be beneficial for acute exacerbation of chronic obstructive pulmonary disease (AECOPD) patients to receive interventions during AECOPD-RW. During exacerbations the treatment principle is to eliminate exogenous pathogens, whereas the AECOPD-RW treatment principle focuses on enhancing body resistance.

**Methods/Design:**

A prospective, multi-center, single-blinded, double-dummy and randomized controlled clinical trial is being conducted to test the therapeutic effects of a sequential two stage treatment, which includes eliminating pathogen and strengthening vital qi with syndrome differentiation. A total of 364 patients will be enrolled in this study with 182 in each treatment group (TCM and control). Patients received medication (or control) according to their assigned group. TCM for AECOPD were administered twice daily to patients with AECOPD over 7 to 21 days, followed by TCM for AECOPD-RW over 28 days. All patients were followed for six months. The clinical symptoms, the modified medical research council dyspnea (MMRC) scale and exacerbations were used as the primary outcome measures. Pulmonary function, quality of life and mortality rate were used as secondary outcome measures.

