### Objective

The objective is to determine whether sequentially eliminating pathogens and strengthening vital qi treatment with syndrome differentiation reduces COPD exacerbation frequency.

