### Sample size

The sample size calculation is based on the effect size of clinical symptom changes in AECOPD subjects from a previous trial of one of the most commonly used TCM injections [12]. In that study, the mean effective change in clinical symptoms was 97% in the treatment group, compared to 87% in the placebo group (*P *< 0.05). For the proposed study, to achieve a similar difference between the TCM and placebo treatment groups with an 90% power and a two-tailed significance level of 5%, *n*_1 _= *n*_2 _= 1,641.6 × [[]]^2^, the sample size in each group is 145. Considering a 20% drop-out rate over the course of the study, 182 patients will be enrolled in each group, that is, 364 in total. Intention-to-treat analysis will be applied to minimize bias due to drop-outs.

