### Statistical analysis

A descriptive statistical analysis will be performed for all study variables. We will calculate the mean, median and standard deviations for quantitative variables, and the absolute and relative frequency for qualitative variables.

We will use SPSS 19.0 (License number: 6f1d84c801f1e6010dc, SPSS Inc. Chicago, Illinois state, United States) to statistically analyze the data. An intention-to-treat analysis will be applied using the Last Observation Carried Forward (LOCF) method for missing data. Analysis of covariance with baseline as covariate will be used to assess differences in treatment outcomes between the two groups at each of these time points. To correct for inflated risk of Type 1 error, multiple comparison procedures suggested by Ludbrook et al. will be used [14]. The use of relief medication during the trial will be investigated for its effect on the outcome measures by using it as a covariate in the statistical analysis. A Data Safety Monitoring Board has been established to assess the progress of the trial, particularly safety endpoints.

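### Three primary outcomes tested at repeated visits call for the promised Type 1 error correction, but the 90% power is for one uncorrected 5% test of symptoms, not for exacerbation frequency

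*Protocol article*

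**What the plan says.** **Outcomes.** The abstract (Methods/Design) states: "The clinical symptoms, the modified medical research council dyspnea (MMRC) scale and exacerbations were used as the primary outcome measures". The body agrees. Under Outcome measurements, the sections on exacerbations, on symptoms and signs, and on dyspnea all come before the heading for secondary outcomes.

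**Question.** The Objective is to find out whether sequential elimination of pathogens and "strengthening vital qi treatment with syndrome differentiation reduces COPD exacerbation frequency". The hypothesis at the end of the Background is equally narrow.

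**Sizing.** "The sample size calculation is based on the effect size of clinical symptom changes in AECOPD subjects", taken from a previous trial in which "the mean effective change in clinical symptoms was 97% in the treatment group, compared to 87% in the placebo group". The calculation is made "with an 90% power and a two-tailed significance level of 5" per cent. It gives 145 per group, raised to 182 for 20% drop-out, 364 in total.

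**Analysis.** The Statistical analysis section plans intention-to-treat with LOCF and an analysis of covariance between the groups at each time point. It continues: "To correct for inflated risk of Type 1 error, multiple comparison procedures suggested by" a cited reference.

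**The concern.** The sections do not describe the same trial. The outcome list gives three ways to a primary result, each read at several visits. The objective gives one question. The sample size spends the whole 5% on one comparison, and that comparison is a symptom response rather than the outcome in the objective. The analysis section accepts that the error rate is inflated and promises a correction, but the sample size is not calculated at a corrected level.

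Two things are at stake. The advertised 90% may not describe the tests that will be run. And the article gives no rule for a split result, such as a gain on early symptom readings with nothing on exacerbation frequency, where readers could disagree on whether the trial met its aim.

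**Working it through.** **Inputs.** Rates 97% and 87%, two-sided 5%, 90% power, 145 per group and 20% drop-out (Sample size); 1:1 allocation and 12 visits (Study design); visit schedules (Outcome measurements).

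**1. The plan's own figure.** The bracketed part of the formula is lost in the text, but the constant 1,641.6 belongs to the arcsine formula in degrees:

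n = 1641.6 × [(z_α/2 + z_β) / (arcsin√p1 − arcsin√p2)]²

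- arcsin√0.97 = 80.03°, arcsin√0.87 = 68.87°, difference 11.16°
- n = 1641.6 × (3.2415 / 11.16)² = 138.5, so 139 per group

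The stated 145 is not matched exactly, but rates of 96.67% and 86.67% would give 145.2, so rounding of the rates explains the gap and nothing below depends on it. The rest reproduces: 145 / 0.8 = 181.25, so 182 per group, and 2 × 182 = 364.

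**2. Count of comparisons.**

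- Symptoms: days 4, 7, 14, 21, four weekly visits, months 1, 3, 6: 4 + 4 + 3 = 11. With day 0 this is 12, as in Study design.
- MMRC: weekly on treatment (up to 3 + 4), then three follow-up visits: 10.
- Exacerbations: months 1, 3, 6: 3.
- Total: 11 + 10 + 3 = 24. This is a maximum, because exacerbation treatment may last only 7 days.

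**3. Power of the sizing comparison.**

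- Arcsine: Φ(11.16 × √(n/1641.6) − z_α/2)
- Pooled: Φ([0.10 − z_α/2 × √(2 × 0.92 × 0.08/n)] / √[(0.97 × 0.03 + 0.87 × 0.13)/n])

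Example with the arcsine form at n = 145: 11.16 × √(145/1641.6) = 3.317. Subtracting 1.960 gives 1.357 and 91.3%. Subtracting 2.394 (α = 0.05/3) gives 0.923 and 82.2%.

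| Two-sided α | 145 per group, arcsine / pooled | 182 per group, arcsine / pooled |
|---|---|---|
| 0.05, uncorrected | 91.3% / 88.5% | 96.0% / 94.3% |
| 0.05/3 = 0.0167 | 82.2% / 77.6% | 90.7% / 87.3% |
| 0.05/24 = 0.0021 | 59.4% / 52.5% | 73.8% / 67.2% |

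The first row at 145 brackets the stated 90%.

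**4. Size needed to keep 90% over three outcomes.** At α = 0.0167 the two formulas give 179 or 197 per group. Dividing by 0.8 gives 224 or 247 enrolled per group, against 182.

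**5. Exacerbation frequency.** The article gives no event rate, no assumed reduction and no variance, so no power can be computed for it.

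**The case against.** **The error rate is addressed.** A reader might infer that the plan runs at a family-wise error of about 14% (1 − 0.95³ = 0.143 for three independent tests). It does not say so: the Statistical analysis section commits to a correction. The 14% describes an uncorrected plan that the article does not contain. This objection stands in full.

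**Error rate and power can coexist.** A reader might also infer that 5% and 90% cannot both hold. That is too strong. The plan is intention-to-treat with LOCF, so up to 182 per group may be analysed, and Bonferroni over three outcomes then leaves 90.7% by the arcsine form, the one the protocol's constant belongs to. A fixed order with one lead test would also keep both for that test. This stands, with two limits. The protocol itself sets 145 as the number needed and adds the rest for drop-out. And if the correction also spans the time points, even 182 gives at most 74%.

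**Bonferroni over 24 is a worst case.** The repeated readings are correlated, 24 is a maximum, and the cited procedures may be less strict. This stands, and the 24-comparison row is an outer bound only.

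**Details may sit in the full protocol or analysis plan.** Silence on the primary visit and on the family to be corrected is no fault in an article, and it is not the point here. The point is what the article does state: a sample size at an uncorrected 5%, on an outcome other than the one in the objective.

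**The aims are wider than the Objective.** The Discussion part of the abstract also mentions duration of exacerbation, symptoms and quality of life. That softens the contrast but supplies neither a lead outcome nor power for exacerbation frequency.

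**Conclusion.** The concern holds in a limited form. The stated 90% is not supported after the correction that the plan promises, and it was never shown for the outcome in the Objective. For the symptom response, power after Bonferroni over three outcomes is 78% to 82% at 145 per group and 87% to 91% at 182. Over all 24 comparisons it is 52% to 59% and 67% to 74%. These figures assume true rates of 97% and 87%. The figures at 182 also assume that those rates still hold once missing data are filled in by LOCF.

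The documents do not show an uncontrolled error rate, and they do not show that 5% and 90% are incompatible. They do show a sample size that matches neither the planned correction nor the stated question.

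**What to change.** - Name the exacerbation rate over the whole follow-up as the single primary outcome, tested once at two-sided 5%. This matches the Objective.
- Test the symptom score and then MMRC, each at one stated visit, in fixed order after it. Each is tested only if the one before is significant. Treat all other time points as descriptive.
- In Sample size, state that the 90% applies only to the symptom response at an uncorrected 5%. In the fixed order that test is reached only after a significant exacerbation result.
- Also state there, under declared assumptions on event rate and variability, the difference in exacerbation rate detectable with the planned 364 patients. No extra enrolment is asked for.
- Carry the same hierarchy through the abstract, Outcome measurements and Statistical analysis.

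**Cost.** An amendment to the text and one further calculation. Symptoms and MMRC lose stand-alone primary status, and the calculation may show that 364 patients detect only a large exacerbation difference. Since 105 patients had been recruited at submission, the change must be dated and documented as made before unblinding.

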**Discussion:**

It is hypothesized that sequentially eliminating pathogens and strengthening vital qi treatments with syndrome differentiation will have beneficial effects on reducing the frequency and duration of acute exacerbation, relieving symptoms and improving quality of life for COPD patients.

**Trial registration:**

This study is registered at ClinicalTrials.gov, ChiCTR-TRC-11001460.

## Background

Chronic obstructive pulmonary disease (COPD) is characterized by acceleration in the normal decline in lung function with age and by repeated exacerbations. These exacerbations are associated with worsening symptoms and lung function [1]. The frequency of exacerbation has been shown to be an important determinant of the impaired health-related quality of life seen in COPD patients [2] and to affect decline in lung function [3]. Exacerbations are a frequent cause of physician consultation in primary and secondary care and a major cause of hospital admission and death [4]. Therefore, the management of exacerbations places a considerable burden on the health services both in terms of physician consultation time and healthcare cost [5]. A reduction in exacerbation frequency would have a number of benefits for patients and health services alike [6]. Therefore, preventing exacerbations is a key treatment goal.

The global initiative for chronic obstructive lung diseases (GOLD) document suggests a follow-up at four to six weeks after a hospitalized exacerbation [7]. However, there is evidence that exacerbations tend to cluster in time, with a high-risk period of recurrence during the eight weeks following the first exacerbation [8]. This has important implications for the target of preventative interventions. Therefore, from our clinical observation, we have identified an acute exacerbation of chronic obstructive pulmonary disease risk-window (AECOPD-RW); that is the period after a first exacerbation and before the patient has returned to baseline. During this period, although major symptoms have been relieved, lung function has not gone back to stable baseline, and inflammation may also continue. Therefore, patients may be at increased risk of a second exacerbation, leading to hospital admission and a high mortality rate. Thus, it seems appropriate to intervene in the AECOPD-RW.

Traditional Chinese medicine (TCM) is commonly used for COPD in Asia. It has long been known that TCM is effective in relieving symptoms, reducing the incidence of COPD exacerbations and improving quality of life in COPD patients.

Our previous study showed that in an exacerbation period the treatment principle was to eliminate exogenous pathogens. When the patient enters the AECOPD-RW, the treatment principle should be supporting body resistance [9].

Our hypothesis was that a sequential TCM treatment aimed at eliminating pathogens and strengthening vital qi with syndrome differentiation may reduce exacerbation frequency in patients with AECOPD. In this paper, we report the protocol on a multi-center, randomized, single-blind, placebo-controlled trial to test this hypothesis.

### Objective

The objective is to determine whether sequentially eliminating pathogens and strengthening vital qi treatment with syndrome differentiation reduces COPD exacerbation frequency.

## Methods and design

### Study design

This clinical trial is multi-centered, randomized, single-blind and placebo-controlled. The design of the study integrates rigorous, contemporary clinical research methodology in accord with principles set out in the Declaration of Helsinki and the Good Clinical Practice guidelines regarding the appropriate use of TCM in clinical practice. Reporting will be guided by the CONSORT statement [10,11]. Subjects are being enrolled at eight hospitals in four sites in China: 1) The First Affiliated Hospital of Henan University of TCM; 2) TCM hospital of Xinjiang Uygur Autonomous Region; 3) Sichuan Province TCM hospital; 4) Jiangsu Province Hospital of TCM; 5) the First Affiliated Hospital of Henan University of Science and Technology; 6) Henan University of Huaihe hospital; 7) The First Affiliated Hospital of Zhengzhou University; and 8) Henan Provincial Chest Hospital. The eight hospitals in China will randomly assign 364 patients with AECOPD in a ratio of 1:1 to the TCM treatment group or matching placebo. Consenting eligible participants will be enrolled for five to eight weeks and required to attend 12 visits in total. The trial has three phases: one to three weeks treatment with either TCM for AECOPD or placebo granules, four weeks treatment with either TCM for AECOPD-RW or placebo granules, and six months follow-up (Figure 1).

**Figure 1 F1:**
[figure not shown]
**Participation flow chart**.

### Study duration

Ongoing recruitment will occur for a maximum period of 18 months (between July 2011 and December 2012) or until 364 individuals are randomized.

### Subjects

A total of 364 participants will be recruited through local advertising and doctor referrals from hospital outpatients and general practice clinics. Interested participants can telephone or email the trial coordinators at the corresponding sites for further information. Participant information and consent forms will be sent to interested individuals to be read prior to scheduling their first visit.

### Inclusion criteria for participation in the trial

The inclusion criteria are as follows: 1) males and females aged 40 to 80 years inclusive; 2) they must satisfy the COPD diagnostic criteria defined by GOLD (post-bronchodilator spirometry, forced expiratory volume in 1 second (FEV_1_)/forced vital capacity (FVC) < 0.7 and predicted FEV_1 _50% to 80%); 3) they must experience an acute infective exacerbation of COPD; 5) meet the TCM diagnostic criteria (syndrome of exogenous cold-evil and internalization, syndrome of accumulation of phlegm-dampness in the lung, syndrome of phlegm-heat obstructing in the lung); and 6) give written informed consent to participate.

### Exclusion criteria

Exclusion criteria include: 1) pregnancy, breast-feeding or women intending to become pregnant during the course of the study; 2) inability to understand the nature, scope and possible consequences of the study; 3) diagnosis of bronchiectasis or active tuberculosis, obliterative bronchiolitis or diffuse pantothcnic bronchiolitis, pneumothorax, pleural effusion or pulmonary embolism; 4) a history of bronchial asthma or neuromuscular disorder that affects respiration; 5) cancer; 6) respiratory failure that needs mechanical ventilation; 7) serious illnesses, such as heart, liver or kidney diseases, or unstable hemodynamics; 8) inability to adequately perform spirometry tests; 9) need for long periods of bed rest; 10) on long-term immunosuppressive agents or immunostimulants; 11) an allergic history to TCM products or participating in other trials.

This study will be conducted in accordance with protection of patients, as outlined in the Declaration of Helsinki. Each participant will sign the written informed consent before undergoing any examination or study procedure, in compliance with Good Clinical Practice. Patients whose syndrome differentiation of TCM is the syndrome of exogenous cold-evil and internalization, syndrome of accumulation of phlegm-dampness in the lung or syndrome of phlegm-heat obstructing in the lung are included. Patients who initially meet eligibility criteria will complete the additional baseline testing and will be randomized into either the treatment or the control group.

### Ethics issue

This study has been approved by the Ethics Committee of The First Affiliated Hospital of Henan University of TCM (No: YFYKYLL2011-001). Each participating center obtained a local Institutional Review Board Approval. All study participants will sign the written informed consent prior to participation.

### Interventions

Eligible patients will be randomized to one of the two arms: placebo or Chinese medical herb (11.65 g twice daily). Three TCM formulas for exacerbation will be administered orally for 7 to 21 days: sanhanhuayinfang (*Ephedra, Rumulus Ginnamomi, Rhizoma Zingiberis*, and so on), qingrehuatanfang (*Mongolian snakegourd fruit, Rhizoma Pinelliae, Bulbus Fritillariae Cirrhosae *and so on), zaoshihuatanfang (*Prepared Pinellia Tuber, Officinal Magnolia Bark, Tangerine Peel *and so on). There are also three TCM formulas for AECOPD-RW that will be administered orally for four weeks; they are: bufeijianpifang (*Codonopsis, Astragalus root, Largehead Atractylodes Rhizome, Perilla Fruit, Mangnolia officinalis*, and so on), bufeiyishenfang (*Ginseng, Astragalus root, medlar *and so on), yiqizishenfang (*Ginseng, solomonseal, Rehmannia Glutinosa *and so on). All drugs were made into granules by Jiangyin Tianjiang Pharmaceutical Co., Ltd. Jiangyin city, Jiangsu province, China). In this study, the subjects and statisticians will be blinded to treatment assignment. In this respect, the trial is single-blind. Randomization of subjects will occur centrally using a random number generator and will be stratified by syndrome differentiation of TCM. (Syndrome, as related to illnesses in Western medicine, is composed of a set of signs and/or symptoms classified by Traditional Chinese Medicine practitioners. TCM Syndrome differentiation is based on symptoms and helps to identify a subset of disease). Patients will visit the doctor at one-, three- and six-month follow-ups.

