### Randomization and allocation

Treatment allocation occurs when the study participant meets the inclusion criteria and signs the informed consent form. The teletherapist will then register the participant into the database, which, in turn, asks if they are ready to be randomized. After the teletherapist enters Yes, the site-specific randomization program displays the participant's group assignment number (placebo versus Chinese medical herb). Site-specific randomization lists will be computer-generated (that is, generated by an individualized basic visual code program) and concealed from the researchers by a senior data manager, who is not involved in the study. This information will remain confidential and is not shared with the study sites, in concordance with the CONSORT guidelines. This trial uses a prospective, randomized, outcome-blinded design, in which all outcome assessments are made by a research assistant blinded to treatment allocation and uninvolved in patient consent and management. The allocation list will be protected by password access files and held by an independent non-investigator. In the event of a clinical emergency, the individual's randomization code and group allocation can be identified.

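### The stated ANCOVA names neither TCM syndrome nor site, the factors that randomisation uses; if they are prognostic, precision is lost and the test may be mildly conservative

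*Protocol article*

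**What the plan says.** The protocol article describes the allocation scheme in two places.

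- **Interventions:** "Randomization of subjects will occur centrally using a random number generator and will be stratified by syndrome differentiation of TCM". Three syndromes are eligible.
- **Randomization and allocation:** "Site-specific randomization lists will be computer-generated". Syndrome is not mentioned here. Neither section gives a block size or any other restriction within a list.

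On the meaning of site, Study design says "Subjects are being enrolled at eight hospitals in four sites in China" and then names eight hospitals.

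The Statistical analysis section fixes the method for comparing the groups at every assessment: "Analysis of covariance with baseline as covariate". It names one other covariate: "The use of relief medication during the trial will be investigated for its effect on the outcome measures by using it as a covariate". Relief medication is recorded after randomisation. Syndrome and site do not appear in the analysis.

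**The concern.** A model is normally expected to contain the factors that restricted the randomisation. When allocation is balanced within prognostic strata, the treatment estimate is free of the between-strata variation. A model without the strata still counts that variation as error, so its standard error describes a noisier estimate than the trial produces. Confidence intervals are then too wide and tests too cautious.

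It is plausible that these factors are prognostic. The article says syndrome differentiation rests on symptoms and picks out a subset of disease, and symptoms are among the primary outcomes. Hospitals may also differ in how they record symptoms and exacerbations. At stake is precision at a fixed sample size, and agreement between the design and its inference. As written, the plan names a post-randomisation covariate and leaves out the factors that randomisation uses.

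**Working it through.** **Reference point from the plan.** The Sample size section rests on this: "the mean effective change in clinical symptoms was 97% in the treatment group, compared to 87% in the placebo group", "with an 90% power and a two-tailed significance level of 5"%. It states 145 per group, and 182 after 20% drop-out.
- Drop-out step: 145 / 0.8 = 181.25, so 182. This reproduces.
- The constant 1,641.6 points to the arcsine formula in degrees. The angles are 80.03° and 68.87°, a difference of 11.16°. Then n = 1,641.6 × (3.242 / 11.16)² = 138.5, so 139, not 145. Power at 145 is 88.5% (pooled test) or 91.3% (arcsine). This small gap is a separate matter. It only shows that 90% is a fair reference for what follows.

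**Inputs.**
- Syndrome: 3 levels (Inclusion criteria).
- Site: 4 or 8 levels (Study design). That makes 3 × 4 = 12 or 3 × 8 = 24 cells, so 364 / 12 ≈ 30 or 364 / 24 ≈ 15 patients per cell on average.
- R²: the share of outcome variance left after baseline that syndrome and site explain. The documents give no value, so a range is assumed.

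**Formulas for a linear model with allocation balanced within strata.**
- Reported SE / correct SE: k = 1/√(1 − R²)
- Actual type I error without strata terms: 2 × [1 − Φ(1.96 k)]
- Power without strata terms, for a comparison sized at 90%: Φ(1.2816 k)
- Power with strata terms: Φ(3.2415 k − 1.96)
- Equivalent patients per arm: 145 × R²

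| Assumed R² | k | Type I error | Power without | Power with | Gain (points) | Patients per arm |
|---|---|---|---|---|---|---|
| 0 | 1.000 | 0.050 | 0.900 | 0.900 | 0 | 0 |
| 0.02 | 1.010 | 0.048 | 0.902 | 0.906 | 0.3 | 3 |
| 0.05 | 1.026 | 0.044 | 0.906 | 0.914 | 0.8 | 7 |
| 0.10 | 1.054 | 0.039 | 0.912 | 0.927 | 1.6 | 14 |
| 0.15 | 1.085 | 0.034 | 0.918 | 0.940 | 2.2 | 22 |

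**Simulation check.** 290 patients, 8 sites, 3 syndromes, 4,000 runs per setting. R² was set at 0.20, above the range in the table, to make the contrast clear.

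| Allocation | Model | Mean reported SE | True SD of estimate | Type I error |
|---|---|---|---|---|
| Blocks of 4 within strata | Baseline | 0.118 | 0.105 | 0.025 |
| Blocks of 4 within strata | Baseline + site + syndrome | 0.105 | 0.104 | 0.049 |
| Simple randomisation | Baseline | 0.118 | 0.119 | 0.054 |
| Simple randomisation | Baseline + site + syndrome | 0.107 | 0.108 | 0.052 |

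With R² = 0 and blocking, the baseline-only SE was not inflated (0.117 against a true SD of 0.118). The Monte Carlo error on a type I error of 0.05 is √(0.05 × 0.95 / 4,000) ≈ 0.003.

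The two allocations therefore separate. With balance within strata, the baseline-only SE is too wide. With simple random lists it is valid, but the estimate is less precise than it could be (0.119 against 0.108).

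**The case against.** The strongest reply is that the documents do not establish a wrong standard error. That needs balanced allocation and strata that predict outcome beyond baseline, and neither is documented. This stands. A reader might infer that the trial's standard errors are too wide and its real type I error is below 5%. The text does not support that as fact: with simple random lists the baseline-only SE is correct, and with R² = 0 nothing is inflated under either scheme.

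Three further points stand:
- The R² that matters is the share left after baseline. For symptom outcomes, baseline may already absorb part of what syndrome carries.
- A reader might compare the adjusted power of 91% to 94% (R² of 0.05 to 0.15) with the planned 90%. Under balanced allocation that is the wrong comparison, because the unadjusted test is itself already at 90.6% to 91.8%.
- The sizing compares proportions, so these linear-model figures are indicative for the ANCOVA and do not carry over directly to that comparison.

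It can also be said that an unseen analysis plan may add the terms. It may. But this article does not leave the covariates open: it names baseline and relief medication. It also describes the randomisation scheme in two ways that do not match, so an analyst could not tell from it which terms reflect the design.

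**Conclusion.** The point holds as a modest question of efficiency and consistency. Syndrome and site shape the allocation and are absent from the stated model. If they are prognostic beyond baseline, precision is lost under either form of allocation. If allocation is also balanced within strata, the reported standard error is conservative by about 1% to 8% and the type I error is about 4.8% to 3.4%, with a power gain from adjustment of up to about 2 points. These figures rest on an assumed residual R² of 0.02 to 0.15 and on a linear model.

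The treatment difference is not biased and false positives are not inflated, so this does not threaten the validity of a positive result. The mismatch between the scheme and the model can be read from the text with confidence. Its size cannot.

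**What to change.** 1. In Statistical analysis, add TCM syndrome at randomisation (3 levels) and the site unit used for the lists as covariates in the planned treatment comparisons. Site can be fixed, or random or pooled where centres are small. This takes 2 + 3 = 5 degrees of freedom with four sites, or 2 + 7 = 9 with eight hospitals, which is little against 290 analysed patients (2 × 145).
2. Reconcile Interventions with Randomization and allocation. State the stratification factors once, say whether site means the four sites or the eight hospitals, and say whether allocation is restricted within each list. The model terms should then match.

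The cost is a sentence in the analysis section and a clarification of the scheme. Both variables are known at randomisation, so no new data are needed. The change should be made before unblinding.
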